### Activity monitoring

Participants aged 13 years and over are asked to wear wearable activity monitor/s each day for up to a week and up to twice within a 12-month period, with at least 6 months between each wear period. The purpose of this stratification is to capture activity during the spring-summer season versus the fall-winter season.

The Especialista and/or research staff dispense the wearable device/s to the participant and train them on how to use the wearables. Participants wear a Fitbit Charge 2™ (Fitbit, Inc., San Francisco, CA) (or a similar Fitbit activity tracker) on the non-dominant wrist and an ActiGraph wGT3X-BT (ActiGraph, LLC, Pensacola, FL) monitor on the dominant hip. Participants are asked to wear the Fitbit at night, and the ActiGraph can be removed at night and replaced in the morning. After dispensing the device/s, each participant or their representative fills in an activity questionnaire to distinguish physical activity relating to the participant’s occupation from physical activity via leisure-time exercise. Participants are asked to return the wearable device/s after one week. Both devices are then downloaded to a computer at the study center; Fitbits are not wirelessly synchronized to a mobile phone application. Adherence is defined as ≥12 h/day of wear time for at least 3 of the 7 days, and the 3 days of wear was chosen to represent approximately half of the possible wear time. Upon return of wearable device/s, each participant or their representative may complete an Activity Monitor Follow-up Survey.

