### Study activity series and scheduling encounters

Study activities take place through face-to-face interaction between families and study staff; these visits are referred to as “encounters.” Encounters are organized into “series,” with activities varying based on whether the series is for a new participant or a continuing participant. Each new participant completes an initial encounter series, including screening/enrollment and informed consent, Health Promotion Assessment (HPA), laboratory tests, questionnaires, and reflection, as well as physical activity monitoring and interaction with the Especialista with whom they are paired. After having been enrolled in the study for at least 12 months, participants are eligible to start the continuing participant encounter series. The continuing participant encounter series involves activities similar to the new participant encounter series. While continuing participation is preferred, it is not required to be eligible for the study.

In the course of this 3-year protocol, participants will complete at least 1 new participant encounter series and, possibly, 0, 1, or 2 continuing participant encounter series, depending on their initial enrollment date. Regardless of series type (new participant or continuing participant), participants have the flexibility to complete encounters in accordance with their personal schedules as long as encounter series are completed in chronological order. The last encounter, Reflection, in a 12-month participation cycle occurs at least 3 months after the HPA encounter.

Families may attend study encounters as a group, but individual data collection and informed consent occurs one-on-one in a private setting, unless the participant is a minor. As detailed above, participants are assigned to a data collection group based on their age and diabetes status.

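### The 6-month minimum gap between activity-monitor weeks does not ensure one wear in each season, which is its stated purpose

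*Protocol article*

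**What the plan says.** The Activity monitoring section of the Protocol article asks participants aged 13 and over to "wear wearable activity monitor/s each day for up to a week". They may do this "up to twice within a 12-month period, with at least 6 months between each wear period". The next sentence gives the reason: "The purpose of this stratification is to capture activity during the spring-summer season versus the fall-winter season". The section does not say when either season begins or ends, sets no calendar window for either wear, and limits the gap from above only through the 12-month period.

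The section on the study activity series and scheduling encounters does not fix the dates either. It says that "participants have the flexibility to complete encounters in accordance with their personal schedules as long as encounter series are completed in chronological order". The only interval it sets within a cycle concerns another encounter: "The last encounter, Reflection, in a 12-month participation cycle occurs at least 3 months after the HPA encounter". A cycle's encounters can therefore be finished before a 6-month gap has elapsed, and no encounter pins down the date of the second wear. Taking part beyond the first series is optional ("While continuing participation is preferred, it is not required to be eligible for the study").

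Activity level is one of the four items listed under Major secondary outcomes. The Data analysis section provides in general terms for exploring likely confounders, and for propensity-score matching and regression. It does not name season.

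**The concern.** The scheduling rule and its purpose stand in adjacent sentences, and the rule does not secure the purpose. With two half-year seasons, a gap of exactly 6 months always puts the second wear in the opposite season. Once the gap is longer, some pairs return to the season in which they began, and the share grows with the gap. The rule sets the lower end of the gap and leaves the upper end to the 12-month period.

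Two things are at stake. First, a person with both wears in one season contributes nothing to a within-person seasonal contrast, and no later modelling can supply it. Second, comparisons of activity between groups or along a determinant will mix seasons unevenly. At the least this adds noise. If wear season is related to the exposure being compared, it adds bias. Device-reported sleep comes from the same wear weeks and is affected in the same way.

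**Working it through.** The article gives no figure on this point, so there is nothing to reproduce. The check is of calendar logic.

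**Inputs from the article (Activity monitoring).** Wear lasts up to one week; there are at most two wears in 12 months; the spacing is "with at least 6 months between each wear period"; the purpose is to contrast two seasons.

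**Assumptions, because the article is silent.** (a) The seasons are two contiguous half-years, for illustration April to September and October to March. (b) First-wear dates are spread evenly over the year. (c) The gap distribution is unknown, so a range is shown.

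**Formula for a fixed gap.** Let g be the start-to-start gap in months, 6 ≤ g ≤ 12, and let t be the position of the first wear within its own season, uniform on 0 to 6. The second wear lies at t + g. It is back in the first wear's season when t + g ≥ 12, that is, when t ≥ 12 − g. Hence

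P(same season) = [6 − (12 − g)]/6 = (g − 6)/6.

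| Gap (months) | Same-season share |
|---|---|
| 6 | 0% |
| 6.5 | 0.5/6 = 8% |
| 7 | 1/6 = 17% |
| 8 | 2/6 = 33% |
| 9 | 3/6 = 50% |
| 10 | 4/6 = 67% |
| 11 | 5/6 = 83% |

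A simulation of 2,000,000 first-wear dates agreed with the formula at each gap.

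**Overall share.** The formula is linear in g, so the overall share is (mean gap − 6)/6.

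- Gaps uniform on 6 to 7 months: mean 6.5, share 0.5/6 = 8%.
- Gaps uniform on 6 to 9 months: mean 7.5, share 1.5/6 = 25%.
- All date pairs in a 12-month cycle that are at least 6 months apart equally likely: the density of g is proportional to 12 − g on 6 to 12, so the mean is 8 and the share 2/6 = 33%.
- Gaps uniform on 6 to 12 months: mean 9, share 3/6 = 50%.

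**Tightest literal reading.** If 6 full months must lie between the end of one wear week and the start of the next, the shortest start-to-start gap is 6 + 7/30.4 = 6.23 months. The share is then 0.23/6, about 4%, even if every second wear is booked on the first permitted day.

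**A compliant pair that misses.** Wears on 26 August and the following 6 April are 224 days, or 7.4 months, apart. They meet the rule, and both fall in April to September.

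**The case against.** **The rule often works.** Someone might infer that the wears fall in opposite seasons only when the gap is exactly 6 months. That is true of the guarantee but not of the outcome: 83% of pairs at 7 months and 67% at 8 months still span both seasons. If staff book the second wear as soon as it falls due, few pairs miss. This stands. It is why the point is that the rule does not ensure its purpose, and why the size is given as a range. A single figure near 50% would rest on long gaps being as common as short ones, for which the article gives no basis.

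**Confounding is not shown.** A reader might go on to infer that the activity outcome is confounded with season. The article does not support that. Confounding needs wear season to be associated with the determinant or group compared. No section shows this, and the recruitment channels listed under Setting and participants are not tied to any time of year. Relatives with and without diabetes live together and may attend encounters as a group, which would tend to put them in the same season. If wear dates are unrelated to exposure, season adds noise and not bias. This stands too.

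**Voluntary participation and a condensed article.** Allowing a single wear is ordinary in a voluntary cohort. The covariate list for activity models belongs to an analysis plan that is not shown, and season can be read off the wear date. Neither is an error here.

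**The purpose may be meant for the cohort.** Rolling enrolment would yield wears in both seasons across participants, and no within-person seasonal contrast is listed as an outcome. But the purpose sentence explains the spacing of one person's two wears, and that spacing would do little if only cohort coverage mattered. The mismatch between the rule and its stated purpose therefore remains.

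**Conclusion.** The point holds in a limited form. As written, the spacing rule does not ensure one wear per season. Under half-year seasons and evenly spread first wears, the same-season share of compliant pairs is about 8% for gaps uniform on 6 to 7 months, 33% for equally likely admissible pairs and 50% for gaps uniform on 6 to 12 months. Where the study falls in that range depends on booking practice, which the article does not describe.

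The consequence is an incomplete within-person seasonal contrast, and possible seasonal noise in a major secondary outcome. Bias is conditional on a link between wear season and exposure that the article neither shows nor rules out. The primary outcome, establishing the cohort, is unaffected.

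**What to change.** In the Activity monitoring section, define the two half-years by date. Keep the spacing, but schedule the second wear in the half-year opposite to the first, at about 6 months (for example 5 to 7 months), instead of at any time after 6 months.

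Both parts are needed. Calendar windows alone would accept a wear in late September and another in early October, about a week apart and with no real seasonal contrast. A strict 6-month minimum combined with a season target would leave almost no room for a person first measured at the end of a season: with the first wear at position t months into its half-year, the bookable interval is 6 − t months. With 5 to 7 months it is never shorter than 1 month. The interval runs from the later of 5 and 6 − t to the earlier of 7 and 12 − t, which gives 1 month at t = 0 and at t = 6, and 2 months for t from 1 to 5.

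In the analysis, derive season from each wear date, including for people with one wear. Use it as an adjustment variable in the activity and sleep models. Estimate the seasonal contrast only in people with one wear in each season.

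The cost is a sentence or two in the protocol, one derived variable, and slightly less freedom in booking the second wear. Devices, number of wears and sample size do not change.

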### Reflection

Depending on age and diabetes status, participants may complete a brief questionnaire regarding their Mil Familias experience and an additional finger stick HbA_1c_ may be measured. Additionally, participants may be invited to attend a focus group on their Cohort Establishment study experience and recommendations.

### Data collection, data storage, and statistical analysis

#### Determination of sample size

Up to 1200 families will be screened in the Mil Familias Cohort Establishment study. Given anticipated participation of Latino/a people with T2D as well as their family members, up to 6000 participants may eventually form the Mil Familias cohort. Participants are recruited in multiple places and via a variety of methods, resulting in a diverse and heterogeneous cohort.

#### Data collection

A list of proposed variables/measures to be collected during the Mil Familias Cohort Establishment study can be found in Table 1 and Table 2. In the tables:
*Child* refers to participants aged ≥ 7 and < 18 years; adult refers to participants ≥ 18 years.*Par* refers to the parent/guardian providing information on behalf of the participating child.*Opt* refers to items that are optional, i.e., not required.Administration and use of patient-reported questionnaires are subject to copyright and translation timelines and may be excluded in order to proceed.

**Table 1 Tab1:** Intended variables for data collection

Variable	Encounter and/or Intended Tool or Method (Ref.)	1 – Adult with diabetes	2 – Adult w/o diabetes	3 – Child with diabetes	4 – Child w/o diabetes
CHILDREN/YOUTH VARIABLES FOR ALL 5 DETERMINANTS OF HEALTH					
All variables in minors	NSCH: National Survey Children’s Health [13]	–	–	Par	Par
GENETIC INFLUENCES					
Biobank samples					
Blood	Plasma, serum, buffy coat collected via venous draw	Yes	Yes	Opt	Opt
Epithelial cells	Collected via cheek swab	Yes	Yes	Opt	Opt
Saliva	2 ml saliva into vial collected via spitting into a cup	Yes	Yes	Opt	Opt
Microbiome	Stool sample collected at home and mailed to lab	Opt	Opt	Opt	Opt
BIOLOGICAL INFLUENCES					
Family medical history	HPA: Health Promotion Assessment	Yes	Yes	Par	Par
Physiological markers					
HbA_1c_	Blood draw and fingerstick	Yes	Yes	Opt	Opt
Metabolic panel	Blood draw and urinalysis	Yes	Yes	Opt	Opt
Lipid panel	Blood draw	Yes	Yes	Opt	Opt
Vital signs					
Body mass index (BMI)	HPA: Health Promotion Assessment	Yes	Yes	Yes	Yes
Waist circumference	HPA: Health Promotion Assessment	Yes	Yes	Yes	Yes
Blood pressure	HPA: Health Promotion Assessment	Yes	Yes	Yes	–
Heart rate and rhythm	HPA: Health Promotion Assessment	Yes	Yes	–	–
Foot screening	HPA: Health Promotion Assessment	Yes	–	Yes	–
Date of last dental exam	HPA: Health Promotion Assessment	Yes	Yes	Par	Par
Date of last eye exam	HPA: Health Promotion Assessment	Yes	–	Par	–
Neuropathy (Y/N)	HPA: Health Promotion Assessment	Yes	–	Par	–
Retinopathy (Y/N)	HPA: Health Promotion Assessment	Yes	–	Par	–
History					
Medical history	Medical history, including date of diabetes diagnosis	Yes	Yes	Par	Par
Medication history	Medical history and visual inspection of medications	Yes	Yes	Par	Par
Most recent flu shot	Intro. Interview	Yes	Yes	Par	Par
DM-related foot disease	Q-DFD: Quest. for Diabetes-Related Foot Disease [14]	Yes	–	–	–
Women only					
Menopausal status	HPA: Health Promotion Assessment	Yes	Yes	–	–
Pregnancy status	HPA: Health Promotion Assessment	Yes	Yes	–	–
Number of children	HPA: Health Promotion Assessment	Yes	Yes	–	–
Birthweights of children	HPA: Health Promotion Assessment	Yes	Yes	–	–
Type 1 DM in children	HPA: Health Promotion Assessment	Yes	Yes	–	–
Gestational DM	HPA: Health Promotion Assessment	Yes	Yes	–	–
PSYCHOLOGICAL INFLUENCES					
Quality of life	SF-12: Health Survey Short Form [15]	Yes	Yes	–	–
Adverse childhood events	ACES: Adverse Childhood Events Questionnaire [16]	Yes	Yes	–	–
Depression	PHQ-9: Patient Health Questionnaire [17]	Yes	Yes	–	–
Ethnic discrimination	PEDQ-CV: Perceived Ethnic Discrimination Quest [18].	Yes	Yes	–	–
Spirituality	FACIT-Sp-12: Spiritual Well-Being Scale [19]	Yes	Yes	–	–
Diabetes risk perception	RPS-DD: Risk Perception Survey-Developing Diabetes [20]	–	Yes	–	–

*Abbreviations*: *DM* Diabetes mellitus, *HbA*_*1c*_ Hemoglobin A_1c_, *Intro* Introductory, *Opt* Optional, *Par* Participant

**Table 2 Tab2:** Intended variables for data collection, continued

Variable	Encounter and/or Intended Tool or Method (Ref.)	1 – Adult with diabetes	2 – Adult w/o diabetes	3 – Child with diabetes	4 – Child w/o diabetes
BEHAVIORAL INFLUENCES					
Sleep					
Patient-reported	OSQ: Oviedo Sleep Questionnaire [21]	Yes	Yes	–	–
Device-reported	Wearable device (e.g., Fitbit)	Yes	Yes	≥ 13	≥ 13
Physical activity					
Patient-reported	Activity Log	Yes	Yes	–	–
Device-reported	Wearable device (e.g., Fitbit, ActiGraph)	Yes	Yes	≥ 13	≥ 13
Diet					
Tortilla consumption	Intro. Interview, # corn vs. flour eaten daily past 30 days	Yes	Yes	–	–
Sugary drinks	Intro. Interview, BRFSS questions [22]	Yes	Yes	–	–
Eating out	Intro. Interview, NHANES question [23]	Yes	Yes	–	–
Stress	PSS-4: Perceived Stress Scale [24]	Yes	Yes	–	–
Drug abuse	DAST-10: Drug Abuse Screening Test [25]	Yes	Yes	–	–
DM management	DSSCI: Diabetes Symptom Self-Care Inventory [26]	Yes	–	–	–
Family DM management	FSE: Family Self-Efficacy for Diabetes Management [27]	–	Yes	–	–
Foot care	FCCS-FCB: Foot Care Confidence Scale / Behavior [28]	Yes	–	–	–
SOCIAL-ENVIRONMENTAL INFLUENCES					
Socio-demographics					
Age	Intro. Interview/Demographics	Yes	Yes	Par	Par
Gender	Intro. Interview/Demographics	Yes	Yes	Par	Par
Race/ethnicity	Intro. Interview/Demographics	Yes	Yes	Par	Par
Address	Intro. Interview/Demographics/Contacts	Yes	Yes	Par	Par
Phone number	Intro. Interview/Demographics/Contacts	Yes	Yes	–	–
Email	Intro. Interview/Demographics/Contacts	Yes	Yes	–	–
Household size, income	Intro. Interview/Demographics	Yes	Yes	Par	Par
Education	Intro. Interview/Demographics	Yes	Yes	Par	Par
Insurance status	Intro. Interview/Demographics	Yes	Yes	Par	Par
Insurance type/payer	Intro. Interview/Demographics	Yes	Yes	Par	Par
Recent provider visit	Intro. Interview/Demographics	Yes	Yes	Par	Par
Country of birth	Intro. Interview/Demographics	Yes	Yes	Par	Par
Marital status	Intro. Interview/Demographics	Yes	Yes	–	–
Occupation	Intro. Interview/Demographics	Yes	Yes	–	–
Night shifts	Intro. Interview/Demographics	Yes	Yes	–	–
Alcohol, tobacco use	Intro. Interview/Demographics	Yes	Yes	–	–
Acculturation	BASH: Brief Acculturation Scale for Hispanics [29]	Yes	Yes	–	–
Introductory Interview					
DM cause	Intro. Interview: Why is DM common in Latino families?	Yes	Yes	–	–
DM prevention	Intro. Interview: What can prevent DM in Latino families?	Yes	Yes	–	–
DM challenges	Intro. Interview: What difficulties to get help with DM?	Yes	Yes	–	–
Health literacy	SAHL: Short Assessment of Health Literacy [30]	Yes	Yes	–	–
Health numeracy	NVS: Newest Vital Signs [31]	Yes	Yes	–	–
Trust in physician	TPS: Trust in Physician Scale [32]	Yes	Yes	–	–
Social needs stability	SNST: Health Leads Social Needs Screening Toolkit [33]	Yes	Yes	–	–
Food (In)security	FSSM: Food Security Survey Module [34]	Yes	Yes	–	–
Functional support	SSQ6: Social Support Questionnaire short version [35]	Yes	–	–	–
Support structure	mMOS-SSS: Modified Medical Outcomes Study Social Support Survey [36]	Yes	Yes	–	–

*Abbreviations*: *DM* Diabetes mellitus, *HbA*_*1c*_ Hemoglobin A_1c_, *Intro*., Introductory, *Opt* Optional, *Par* Participant

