### Major secondary outcomes

These include (a) achieved HbA_1c_ levels; (b) cardio-metabolic risk including blood pressure, waist circumference, and insulin sensitivity; (c) food security; and (d) activity levels. Details of additional secondary end-points have been published previously (https://clinicaltrials.gov/ct2/show/NCT03830840).

In addition to the variables listed above, we also collect prospective data related to major cardiovascular events (3-point MACE: cardiovascular death, non-fatal myocardial infarction and non-fatal stroke). Data sources include participants and their families, collaborating health centers, and the local provider of in-hospital clinical care. At enrollment, participants provide written, informed consent for Mil Familias researchers to request data from the relevant provider organization’s electronic medical record system on reported clinical events. Additional information are collected on new onset diabetes including gestational diabetes, unscheduled attendances at emergency rooms, and hospital admissions due to uncontrolled diabetes.

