**Participant Groups**

Individual participants are assigned to a data collection group stratified by age and T2D status, as follows. The group serves to identify the type of data collected for that individual.
Group 1 consists of adults aged ≥ 18 years with T2D.Group 2 consists of adults aged ≥ 18 years without T2D.Group 3 consists of children aged ≥ 7 years and < 18 years with T2D.Group 4 consists of children aged ≥ 7 years and < 18 years with T2D without T2D

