### Health promotion assessment (HPA) and biological specimen collection encounter

Height, weight, and waist circumference are measured following the guidelines in the National Health and Nutrition Examination Survey Anthropometry Procedure Manual, January 2016 [10]. Body mass index is then be calculated. Blood pressure is measured following 2017 guidelines set forth by the American College of Cardiology/American Heart Association Task force on Clinical Practice Guidelines [11]. A foot screening is performed by trained Especialistas with medical provider guidance.

In addition, participants meet with qualified, trained study staff and, depending on age, diabetes status, and personal preferences, the following biological specimens may be collected:
Epithelial cell sample via cheek swab to collect genetic material [DNA Genotek, Ontario, Canada, or Salimetrics, Carlsbad, CA, USA]Saliva sample to collect genetic material [DNA Genotek, Ontario, Canada or Salimetrics, Carlsbad, CA, USA]Urine sample to assess protein levels and potential kidney damage (laboratory screening sample)*Stool sample to analyze bacteria lining the digestive tract for microbiome genomic testing [DNA Genotek, Ontario, Canada or Fecal Occult Blood Test, Beckman Coulter, Brea, CA, USA]Finger-stick HbA_1c_ test [Siemens DCA Vantage, Siemens Healthcare, Norwood, MA, USA]

*Note: Urine samples may be collected at the HPA or Laboratory Encounter.

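### Blood pressure belongs to a major secondary outcome stated for all participants, but Table 1 does not collect it in children without T2D, who attend the same assessment

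*Protocol article*

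**What the plan says.** All references are to the protocol article.

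- **Major secondary outcomes.** Outcome (b) is "cardio-metabolic risk including blood pressure, waist circumference, and insulin sensitivity". It is not restricted to any participant group.
- **Data collection, Table 1, vital signs.** The blood pressure row reads "Blood pressure HPA: Health Promotion Assessment Yes Yes Yes", and its last cell is a dash. The last two column heads are "3 – Child with diabetes 4 – Child w/o diabetes", so the dash falls on Group 4. The waist circumference row reads "Waist circumference HPA: Health Promotion Assessment Yes Yes Yes Yes"; BMI has the same four entries.
- **Participant Groups.** "The group serves to identify the type of data collected for that individual".
- **Study activity series and scheduling encounters.** The HPA is part of the initial series for every new participant, and no group is exempted.
- **HPA and biological specimen collection encounter.** "Blood pressure is measured following 2017 guidelines", with no group named. The qualifier in that section, "depending on age, diabetes status, and personal preferences, the following biological specimens may be collected", applies to specimens only.

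The article gives no reason for leaving blood pressure out in Group 4.

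**The concern.** The outcome list and the collection table do not match. The outcome is worded for the whole cohort, but one of its components has no source of data in one of the four groups. Age does not explain the gap, because children with T2D cover the same age range and are measured. Lack of opportunity does not explain it either, because Group 4 is already at the HPA for height, weight and waist.

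Two uses of the data are at stake. The first is cross-sectional: blood pressure in children with T2D would have no counterpart from children of similar age without T2D in the cohort. Adults without T2D are measured, but they differ in age and are no substitute. The second is longitudinal: the study collects data annually for up to 3 years and records new-onset diabetes. A Group 4 child who develops T2D, or who passes 18, would enter that later stage without an earlier study reading. Readings never taken cannot be recovered by a later analysis plan.

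**Working it through.** No formula, sample size or significance level enters this point, and the plan gives no figure to reproduce. The check is a comparison of sections.

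**1. Which groups supply each measure** (Table 1, same encounter)

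| Measure | Adult, T2D | Adult, no T2D | Child, T2D | Child, no T2D | Groups covered |
|---|---|---|---|---|---|
| Blood pressure | Yes | Yes | Yes | – | 3 of 4 |
| Waist circumference | Yes | Yes | Yes | Yes | 4 of 4 |
| BMI | Yes | Yes | Yes | Yes | 4 of 4 |

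For blood pressure, adults can be contrasted by T2D status and children cannot. For waist circumference, which belongs to the same outcome, both contrasts are possible.

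**2. What the dash means.** The table does not define it. Optional items and items reported by a parent have their own codes, so 'not collected' is the natural reading. The row has all its cells, so the dash does not look like a conversion error.

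**3. Whether the dash fits a pattern.** Across Tables 1 and 2, five rows differ between the two child groups:

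| Row | Children split by T2D status | Adults split by T2D status |
|---|---|---|
| Foot screening | yes | yes |
| Last eye exam | yes | yes |
| Neuropathy | yes | yes |
| Retinopathy | yes | yes |
| Blood pressure | yes | **no** |

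The first four concern diabetes complications and are left out for adults without T2D as well. Blood pressure is the only row that separates children by T2D status while treating adults alike. It is also the only one of the five that is named among the major secondary outcomes.

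**4. Whether the dash governs practice.** The groups decide what is collected from each person, so staff following Table 1 would not take the reading in Group 4.

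**5. What can be quantified.** Only the coverage, 3 of 4 groups. The article does not state how many children are expected, how many have T2D, or how many would develop it, so no loss of precision or power can be calculated.

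**The case against.** The strongest case on the other side has four parts.

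*No child comparison is planned.* The groups are defined as data-collection groups, the primary outcome is the creation of the cohort, and the analysis section names general tests only. This stands. A reader might infer that a planned test of children with against children without T2D is defeated, or that a planned parent-child analysis of blood pressure is lost. The article plans neither. The point is a gap between the outcome list and the data collected.

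*The text and the table do not truly conflict.* The same HPA paragraph describes foot screening without naming groups, yet Table 1 limits it to Groups 1 and 3. The prose may simply say how measurements are made and leave the table to say in whom. This largely stands. A reader might treat the HPA sentence as a firm contradiction of Table 1, but it is weak evidence. The mismatch between the outcome list and Table 1 does not need it.

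*Other outcomes are incomplete in children too.* HbA1c is optional in both child groups, food security is collected in neither, and device-reported activity starts at age 13. This is true, but each rule applies equally to both child groups. Only blood pressure is dropped according to T2D status.

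*The longitudinal loss is speculative.* Continuing participation is voluntary, with 0, 1 or 2 further series, and the article does not describe moving participants between groups. This limits the size of the loss. It does not remove it, since annual follow-up and new-onset diabetes are both part of the study. It is also tempting to say that most of the child cohort is affected, but that assumes most enrolled children are free of T2D, and the article gives no figure. If the assumption is right, the smaller Group 3 would limit the precision of any child comparison even with Group 4 measured.

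**Conclusion.** The point holds as a modest design gap that should be corrected. A component of a major secondary outcome, stated without group limits, is not collected in one of the four groups. No reason is given, and the pattern matches no other row of the tables. Followed as written, the cohort would hold no study blood pressure from children without T2D, and no earlier study reading for those who later develop T2D or reach 18.

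This rests on reading the dash as 'not collected' and on Table 1 being applied as printed. It concerns readings taken in the study; a clinic record might hold a value for some children, but Table 1 names the HPA as the source. The size in terms of information lost is unknown, because neither the number of children nor a comparison between the child groups is specified.

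**What to change.** In Table 1, change the Group 4 entry for blood pressure from the dash to 'Yes', or at least to 'Opt'. The cost is a short non-invasive reading per child at an encounter these children already attend, using a procedure already in place for Group 3. It adds no visit.

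If the dash is intended, state under Major secondary outcomes that the blood pressure outcome covers Groups 1 to 3 only and that no comparison of blood pressure by T2D status will be made in children. Align the sentence in the HPA section with that scope. Limiting the outcome to adults would not be a correct alternative, since it would discard the readings planned in Group 3. This option costs only the change of wording, but it leaves the data gap in place.
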